## Abstract

Acquired Brain Injuries are one of the leading causes of mortality and disability worldwide. One of the most frequent sequelae is motor impairment of the upper limbs, which affects people’s functionality and quality of life. Following the discovery of mirror neurons, new techniques were developed based on the mechanisms of neuronal plasticity, such as motor imagery (MI) and action observation (AO). We propose a protocol using electromyographic recordings of forearm muscles in people who have suffered a stroke during an MI task and an AO task. Three different experimental conditions will be studied during the electromyographic recordings: control recording, recording during MI, and recording during AO. Understanding the muscle activation in each technique will allow us to develop future protocols and intervention plans, improving the quality of care for people who have suffered a stroke.

## 1. Introduction

Acquired Brain Injury (ABI) is defined as a sudden injury to the brain, classified as an ischemic stroke (blockage of a blood vessel) or haemorrhagic stroke (rupture of a blood vessel) [1]. The increases in life expectancy and healthcare quality have increased the number of survivors affected by stroke [2,3]. This situation will increase costs associated with service provision and loss of productivity, making studying rehabilitative techniques for improved functional recovery essential.

People who have suffered a stroke may have physical, cognitive, emotional, and social sequelae that alter their functionality and quality of life. Many of these people suffer motor impairments at the level of the upper limbs, which implies severe difficulties in performing activities of daily living (ADLs) [4]. Improving the indication of treatment tools will allow better results to be achieved in increasing these people’s functionality and quality of life.

Rizzolatti’s discovery of mirror neurons in the 1990s was a significant breakthrough in neurorehabilitation [5], as new tools and therapeutic approaches based on neuroplasticity mechanisms appeared. In these tools, the focus is on achieving more direct brain stimulation, achieving motor relearning through the mechanisms of neuronal plasticity. Motor imagery (MI) and action observation (AO) are some of the techniques in this approach. In contrast, other more traditional techniques derived from the bottom-up approach seek to act at the physical level and produce changes at the central nervous system level, such as Vojta or Bobath therapy [6].

MI involves the cognitive task of imagining the realisation of the movement without physically executing it. It is based on the use of cognitive and perceptual processes that results in neural activation similar to that which occurs when the actual execution of the movement or task is performed [7]. Its efficacy in activating cortical and subcortical areas has been demonstrated [8]. However, more evidence must be presented regarding the motor response it elicits. In addition to knowing that the brain areas that are activated during MI are areas related to motor planning, programming, and execution [9], it is of great interest to know the degree of muscle activation and what individual characteristics or determinants modify it during neurorehabilitation.

On the other hand, AO is another rehabilitation tool that facilitates the activation of the motor cortex by activating the mirror neuron system [10]. Studies show that AO facilitates the excitability of the motor system, i.e., facilitates movement execution and motor learning [11]. This tool consists of watching a video showing movements or activities performed in the first or third person. Subsequently, the patient is usually asked to perform the action that has been observed, reinforcing the activation that has occurred at the cortical level.

Studies have focused on the encephalographic activity produced when these techniques are applied [12]. For example, in the case of MI, several studies claim that the frontoparietal, subcortical, and cerebellar regions; the anterior intraparietal cortex; the primary motor cortex; the bilateral supplementary area; and the premotor area are activated [13]. However, the scientific evidence for muscle activation in AO and MI is limited. Other studies confirm that techniques such as MI in neurorehabilitation could be very beneficial because mentally evoking specific movements could lead to functional reorganisation [14].

Most studies focus on the acute phase of the disease. However, analysing what muscle activation occurs in the chronic phase is of great interest. Furthermore, AO and MI are low-cost, easy-to-apply alternatives when other techniques are not possible. When implementing these techniques, it is essential to know the mental evocation capacity of the patients, i.e., their ability to generate mental images. This knowledge is essential as the benefits of these techniques are directly related to this ability [15]. Tools such as the Mental Evocation of Images, Movements and Activities Questionnaire (CEMIMA) can be used to assess mental imagery capacity in individuals with an ABI and evaluate the effectiveness of the applied techniques.

Assessing the muscular response when AO and MI are performed, as well as the individual characteristics of the subjects, will allow us to propose future protocols for stroke patients with motor impairments.

The primary objective of this study is to record muscle activation in the affected upper limb during motor imagery and action observation in people who have suffered a stroke.

The secondary objectives are as follows:To describe the muscle activation in the wrist and finger flexors and extensors that occurs during the use of the CEMIMA as a motor imagery tool via surface electromyographic recordings.To describe, using surface electromyographic recordings, the muscle activation in the wrist and finger flexors and extensors that occurs during the application of action observation.To analyse whether there are differences between the subjects who evoke better or worse mentally depending on their electromyographic response in MI and AO.To analyse the association between the degree of independence in ADLs, upper limb functionality, quality of life, mental evocation, and cognitive impairment with the electromyographic response during MI and AO.To analyse, from a gender perspective, the determinants of the study in men and women.To study whether there is a relationship between the electromyographic response during MI and AO by age or age groups (over 65 years).

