### 2.3. Participants

The study will be carried out on a population of adults with stroke. Subjects will be recruited by convenience sampling through the Rehabilitation Service of the University Hospital of Salamanca and the Salamanca Association of Acquired Brain Injury (ASDACE). Subjects will be asked to participate voluntarily in the study, and once the objectives and content have been explained, they will sign the corresponding informed consent form.

The inclusion criteria are:Being over 18 years of age with an established diagnosis of stroke.Presenting motor response limitations or deficiencies in the upper limbs.Maintaining cognitive functions with the capacity to follow the indications of the interventions and assessments in Spanish language (The Montreal Cognitive Assessment, MoCA > 14).

The following exclusion criteria will be considered: having been diagnosed with mental illness before the stroke; presenting with central nervous system conditions other than stroke or severe or acute cardiorespiratory system disorders; and presenting with fever, muscle inflammation, or myopathies, as well as any vascular and organic insufficiency, liver disease, or skin lesions in the area of application of the electrodes.

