### 2.4. Power Calculation and Sample Size

It is estimated that to conduct a study using linear regression tests for each predictor, considering an effect size between 0.5 and 0.8, a statistical power of 90%, and a safety level of 95% and taking into account the variance of a previous pilot study conducted, between 21 and 28 subjects will be required.

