### 4.3. Data Analysis

The data will be entered into a database, where each subject will be assigned a number and will not be linked to any data that could identify them, guaranteeing their anonymity. Data analysis will be performed by an external statistician using SPSS Statistics for Windows v.28.0 (IBM Corp, Armonk, NY, USA). The most appropriate tests will be established according to the characteristics of the distributions such as descriptive, correlational, and multivariate analyses. An alpha value of 0.05 is established as the level of significance.

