Another strength of this protocol is that it has taken into account certain aspects that have already been demonstrated in other studies. Repeatedly imagining different movements can lead to mental fatigue, affecting motor performance [36]. Therefore, it is essential to control the duration of the recordings and the number of movements and repetitions when designing protocols. In the case of AO, protocols and studies that have been carried out using EMG have shown that muscle activation occurs, and, after training, changes in the contraction of the muscles were studied [37,38]. However, these studies have not been conducted in the therapeutic field, so demonstrating that protocols of this type are effective may open doors in neurorehabilitation.

In terms of limitations, the main limitation may be the number of muscles evaluated, limited by the recording system to be used. It would be interesting to be able to record electromyographic activity in the contralateral limbs. Another limitation may be the convenience sample and its regional context. Furthermore, the heterogenicity of strokes could impact data generalisation. As it is an exploratory intervention, participants adherence can be influenced.

Finally, the analysis of the correlation between the electromyographic response by age may be limited by the smaller number of subjects expected due to the prevalence of stroke in those under 60 years of age.

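### Test evocation ability and age as continuous terms rather than as groups, and adjust the association models for the recorded time since injury

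*Protocol article*

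**What the plan says.** All references are to the protocol article. Its secondary objectives are not numbered; the counts below follow their order in section 1.

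- **Evocation.** The third objective is "To analyse whether there are differences between the subjects who evoke better or worse mentally depending on their electromyographic response in MI and AO". It gives no threshold between better and worse. The fourth objective lists mental evocation again, this time among the factors whose association with the EMG response will be analysed, and with no grouping.
- **Age.** The sixth objective studies the EMG response "by age or age groups (over 65 years"), so grouped and ungrouped forms both stand. Section 5.1 speaks of a correlation with age.
- **Sizing and tests.** Section 2.4 sizes the study at 21 to 28 subjects for linear regression on each predictor, "considering an effect size between 0.5 and 0.8", with 90% power. Section 4.3 leaves the choice of tests to the distributions of the data and adds "An alpha value of 0.05 is established as the level of significance".
- **Time since injury.** Table 1 lists it as a baseline variable. No objective names it, and neither do the lists of determinants in sections 5 and 5.1. The relevant inclusion criterion in section 2.3 is "Being over 18 years of age with an established diagnosis of stroke", with no limit on time since the event. Recruitment is through a hospital rehabilitation service and a patient association.

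**The concern.** CEMIMA is a scaled questionnaire and age comes from date of birth, so both are available as numbers. Cutting either into two groups treats everyone on the same side of the cut as alike, and discards information that a study of 21 to 28 people can hardly spare. A two-group comparison is also not the analysis for which section 2.4 gives a sample size. With grouped and ungrouped versions both open, and the test chosen after looking at the distributions, a reader of the results could not tell which version was meant to carry the conclusion.

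Time since injury is a separate matter and has nothing to do with the power loss. Section 3.2 describes the arm-function test as able to track spontaneous recovery, so the article itself treats one of its predictors as changing with time after stroke. If the EMG response also changes with time (plausible, but not stated), an unadjusted association between arm function or independence and EMG could arise partly because some participants are early and others late in recovery. The variable needed to examine this is already being collected.

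**Working it through.** **Step 1. The plan's own figure.** Section 2.4 gives effect sizes 0.5 to 0.8, 90% power and N of 21 to 28. It does not state the effect-size metric, the number of predictors or the pilot variance. Regression power comes from the noncentral F distribution with noncentrality f² × n, at two-sided 0.05 (sidedness assumed). N needed at 0.5 and at 0.8:

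| Reading of 0.5 / 0.8 | N |
|---|---|
| f², one coefficient | 24 / 16 |
| f², joint test of two predictors | 29 / 20 |
| r, one coefficient | 34 / 9 |
| R², one coefficient | 13 / 6 |
| f, one coefficient | 45 / 19 |

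The joint two-predictor test comes close to 28 / 21, but the article states neither that test nor that number of predictors. The stated range is therefore not reproduced, and any power figure below rests on an assumed reading.

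**Step 2. What a split does.** Take f² = 0.5. Then r = √(0.5/1.5) = 0.577 and r² = 0.333. For normal data, splitting the predictor at proportion p multiplies r by φ(z_p)/√(p(1−p)). At the median this is 0.3989/0.5 = 0.798. The explained variance becomes 0.333 × 0.798² = 0.212, so about 36% of it is lost (1 − 0.798² = 0.36). The equivalent f² is 0.212/(1 − 0.212) = 0.269.

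**Step 3. Power by simulation.** Bivariate normal data, 8,000 runs per row, two-sided 0.05: Pearson test on the ungrouped score against a t test after a median split.

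| n | r | Ungrouped | Median split | Loss (points) |
|---|---|---|---|---|
| 28 | 0.577 | 91.7% | 72.4% | 19.3 |
| 21 | 0.577 | 82.2% | 58.3% | 23.9 |
| 28 | 0.5 | 80.2% | 57.2% | 23.0 |
| 28 | 0.6 | 94.1% | 77.8% | 16.3 |
| 21 | 0.6 | 86.0% | 62.8% | 23.2 |
| 28 | 0.8 | 100% | 98.7% | 1.3 |
| 21 | 0.8 | 99.7% | 94.7% | 5.0 |

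The simulation error on the 72.4% is √(0.724 × 0.276/8,000), about 0.5 points; a repeat with 40,000 runs gave 91.7% and 72.9%. Hence about 92% to 73% at n = 28.

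**Step 4. Cross-check and uneven splits.** The noncentral F treats the predictor values as fixed and so gives somewhat higher power. For f² = 0.5 and n = 28 it gives 95.0% ungrouped, 75.3% at 50/50, 69.9% at 70/30 and 61.4% at 80/20. For n = 21 the figures are 86.7%, 61.7%, 56.3% and 48.5%. The loss grows as the split becomes more uneven. The share of participants over 65 is not known, so none of these can be assigned to the age cut.

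**Step 5. Cost of one covariate.** With f² = 0.5, N for 90% power is 24 whether the model holds one term or two, provided the partial effect is unchanged. If time since injury has correlation ρ with the predictor, the standard error of the predictor's coefficient is multiplied by 1/√(1−ρ²), before any gain from reduced residual variance. For assumed values, ρ = 0.3 gives 1/√0.91 = 1.05 and ρ = 0.5 gives 1/√0.75 = 1.15.

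**The case against.** The strongest reply is that the plan does not confine itself to groups. The fourth objective analyses evocation as an association, age may be used ungrouped, section 5.1 foresees a correlation, and the sizing is by regression. That is correct. A reader might infer that the secondary analyses rest on splits alone; the article does not say so, and the loss applies only where a grouped result is the one relied on. What stands is that the third objective is worded as a group comparison without a cut-off, and that nothing says which form takes precedence.

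The reply also holds that 92% against 73% is not a figure of the plan. That too is correct. It needs f² as the metric, the top of the sample-size range, a median split and normal data. With r = 0.8 and n = 28 the loss is only about 1 point.

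Three further inferences are tempting and not supported:

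- **A second age cut.** Section 5.1 mentions "the smaller number of subjects expected due to the prevalence of stroke in those under 60 years of age". This is a remark on expected numbers and defines no analysis group, so it does not compete with 65.
- **A chronic-phase claim.** The Introduction says that "analysing what muscle activation occurs in the chronic phase is of great interest", but that is one background sentence. The primary objective, eligibility and expected results concern people with stroke in general.
- **Time since injury will never be used.** Section 4.3 foresees multivariate analyses without naming covariates, and a fuller plan may name them. The article supports only that no objective names it.

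Finally, adjustment may cost more than one degree of freedom if time since injury is correlated with the predictors. That stands and is counted in the cost.

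**Conclusion.** The point holds in limited form. The third and sixth secondary objectives admit grouped comparisons of quantities that are available as numbers, in a study sized for regression. Where such a comparison carries the inference, the loss for a median split is about 19 points at n = 28 and 24 points at n = 21 under an assumed r of 0.577, and about 1 to 24 points over the simulated settings (r from 0.5 to 0.8, n of 21 or 28). These are illustrations under bivariate normality and a two-sided 0.05 test, and they do not transfer directly to an age cut at 65.

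Separately, with no time window at entry and time since injury named in no objective, associations of arm function and independence with EMG may partly reflect recovery stage. The size of that confounding cannot be computed from the article. Both matters concern secondary objectives. They are improvements that cost little, and they do not affect the primary recording aim.

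**What to change.** 1. State in the third and sixth secondary objectives, and in section 4.3, that the inferential test uses CEMIMA and age as continuous terms in the regression on which the study is sized. Show better/worse evokers and the over-65 group descriptively only, with the evocation cut-off fixed in advance.
2. Say how the third objective differs from the evocation part of the fourth, or merge them.
3. Include time since injury (for example log-transformed) as a covariate in the association models of the fourth objective, or at least state an adjusted analysis to be reported beside the unadjusted one.

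The cost is a change of wording and no new data: one degree of freedom per adjusted model, plus some precision if time since injury is correlated with the predictor (Step 5 of the working).

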## 2. Experimental Design

### 2.1. Type of Study

A quasi-experimental study will be conducted on a convenience sample under three different experimental conditions.

### 2.2. Study Setting

The study will be conducted at the Faculty of Nursing and Physiotherapy of the University of Salamanca starting 1 January 2024. The protocol for this study was approved by the Salamanca Health Area Drug Research Ethics Committee on 25 September 2023 (CEIm Ref. 2023/09) and follow the guidelines of the Helsinki Declaration. The study is registered at ClinicalTrials.gov, ID: NCT06230718

### 2.3. Participants

The study will be carried out on a population of adults with stroke. Subjects will be recruited by convenience sampling through the Rehabilitation Service of the University Hospital of Salamanca and the Salamanca Association of Acquired Brain Injury (ASDACE). Subjects will be asked to participate voluntarily in the study, and once the objectives and content have been explained, they will sign the corresponding informed consent form.

The inclusion criteria are:Being over 18 years of age with an established diagnosis of stroke.Presenting motor response limitations or deficiencies in the upper limbs.Maintaining cognitive functions with the capacity to follow the indications of the interventions and assessments in Spanish language (The Montreal Cognitive Assessment, MoCA > 14).

The following exclusion criteria will be considered: having been diagnosed with mental illness before the stroke; presenting with central nervous system conditions other than stroke or severe or acute cardiorespiratory system disorders; and presenting with fever, muscle inflammation, or myopathies, as well as any vascular and organic insufficiency, liver disease, or skin lesions in the area of application of the electrodes.

### 2.4. Power Calculation and Sample Size

It is estimated that to conduct a study using linear regression tests for each predictor, considering an effect size between 0.5 and 0.8, a statistical power of 90%, and a safety level of 95% and taking into account the variance of a previous pilot study conducted, between 21 and 28 subjects will be required.

## 3. Materials and Equipment

### 3.1. Variables Study

All study variables are shown in Table 1. In the first column, the baseline variables, including socio-clinical-demographic data of all participants, are shown. The second column presents the primary variables of the study.

### 3.2. Measurement Instruments

Degree of disability and dependence: Barthel Index. This is a generic measure that assesses the level of independence of the patient, allowing the degree of performance of the subject in some basic activities of daily living to be determined, assigning different scores and weightings. It is the most widely used scale internationally for the functional assessment of patients with an acute cerebrovascular pathology and its complications, such as vascular dementia. It includes 10 ADLs: eating, transferring between chair and bed, personal grooming, going to the toilet, bathing/showering, transferring (walking on a smooth surface or in a wheelchair), climbing/descending stairs, dressing, stool control, and urine control [16].Functionality of the upper limbs: Action Research Arm Test (ARAT). This test determines the functionality of the upper limbs after a cortical injury by assessing the ability to manipulate objects of different sizes, weights, and shapes with both hands. It consists of 19 tests divided into four subscales: gross grasp, grasping, pinching, and gross movement. The ARAT takes between 5 and 15 min to administer. It is a reliable and valid measure to assess the motor function of a person who has suffered a stroke. It also allows an assessment of spontaneous recovery and can detect changes that, after intervention, are in the range of clinically significant values [17].Cognitive impairment: Montreal Cognitive Assessment (MoCA). A valid instrument for assessing mild cognitive dysfunction. It consists of the following domains: attention, concentration, executive functions (including the capacity for abstraction), memory, language, visoconstructive abilities, calculation, and orientation. The maximum score is 30. A score of ≥26 is considered normal. Administration time: 10 min [18].Loewenstein Occupational Therapy Cognitive Assessment (LOTCA). This is a standardised occupational-therapy-specific test for use with stroke patients. The LOTCA consists of 20 subtests and assesses four areas: orientation, visual and spatial perception, visual motor organisation, and thinking operations. This test suite is consistent, internally valid, and reliable for determining an initial profile of the cognitive and perceptual abilities of the brain-injured patient [19].Mental evocation capacity: Mental Evocation of Images, Movements and Activities Questionnaire (CEMIMA). The questionnaire consists of two subscales: one of evocation and the other of sensation. It measures the ability to mentally form visual and kinaesthetic images of the hand/upper limb and can also be used to assess the imagination process of the person being assessed. A study of its reliability and validity determined it as an instrument that allows measurements of the ability to mentally form visual and kinaesthetic images of the hand/upper limb and allows an understanding of the imagination process of the person evaluated [20].Perception of quality of life: Stroke Impact Scala 16 (SIS-16). This is a self-report comprising 16 items from four physical domains (strength, hand function, mobility, and ADL/instrumental activities) included in the SIS 3.0. This facilitates its application, as it can be applied in a shorter time, in around 5–10 min [21].
